##### Primary outcome measure

The primary study outcome has been defined as changes in time needed to perform the motor task due to the study intervention. This primary outcome will be assessed by the difference between measurement points T0 and T1. For performance and validity reasons all assessment sessions will be videotaped. Time needed to perform the task in seconds will be derived from the video recordings.

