#### Primary and secondary outcome measures

Table 1 provides an overview on all study outcome measures. All outcome measures will be assessed at four times: twice during the baseline phase (BL, T0), after the intervention (T1), and after the two week follow-up phase (FU). Changes over time will be calculated by the differences between BL vs. T0, T0 vs. T1 and T1 vs. FU.

**Table 1 T1:** Overview study endpoints and outcome measures

	**Primary outcome**	**Primary outcome measure:**
	Time difference between T0 and T1 needed to perform the motor task ('Going down, laying on the floor, and getting up again')	Time will be given in seconds and will be obtained by the recorded video of the task performance.

	**Secondary outcome**	**Secondary outcome measures**

**1**	Time difference between BL vs. T0 and between T1 vs. FU	Time will be given in seconds and will be obtained by the recorded video of the task performance.

**2**	Help needed to perform the motor task	Assistance levels of the activity scale of the Chedoke McMaster Stroke Assessment (CMSA)

**3**	Stage of the motor task	Stage of the motor task by Bergland and Lake will be obtained by the recorded video of the task performance.

**4**	Imagination inflation	Patients will be asked before each motor task execution during the assessments to predict time they expect to need to perform the motor task.

**5**	Motor impairment and independence	German version of the extended Barthel index (EBI)

**6**	Balance	German version of the Berg Balance Scale (BBS)

**7**	Motor imagery ability	German version of the kinesthetic and visual motor imagery questionnaire (KVIQ-G)

**8**	Understanding of the motor imagery instructions	German version of the Imaprax software version 1.1

**9**	Fear of falling (FOF)	German version of the Activities-Specific Balance Confidence Scale (ABC-scale)

**10**	Intrinsic motivation	Motor imagery diary

**11**	Mood	Direct question that can be answered on an 11-point VAS: 'How sad do you feel today?'

All outcome measures will be assessed at four times to measure changes over time: twice during the baseline phase, after the intervention, and after the two week follow-up phase.

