##### Motor task related profile

1. Time difference to perform the motor task between BL and T0 as well as between T1 and FU.

2. Help needed to perform the motor task will be evaluated using classification levels of the activity scale of the Chedoke McMaster Stroke Assessment (CMSA) [40,41]. The CMSA is a validated and very reliable performance-based assessment [42-44]. The activity scale belongs to the gross function index and is scored with one (patient needs total assistance or the task is not tested for safety reasons) to seven (patient can perform the task completely independent without any assistance or devices, in a reasonable time) on an ordinal scale [45].

3. Stage of the motor task will be evaluated using the classification of Bergland and Laake [46] (please see section 'Stages of the motor task').

4. 'Imagination inflation': Undergraduate college students overestimated their motor performance after MI training. This effect is called 'Imagination inflation' and was detected by Landau et al [47]. To monitor the inflation in this investigation all patients will be asked before each motor task execution during the assessments to predict time they will need to perform the task before each motor task execution.

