#### Study procedure and measurement events

The study procedure and all measurement events are illustrated in Figure 1. After signing informed consent, patients will start with the baseline phase that extends over week 1 and week 2. During this time patients will undergo all clinical measurements twice (BL, T0) at an interval of six to seven days. After the baseline phase all patients will be randomised to one of three study groups: EG1, EG2, or CG. Each group will receive three therapy sessions per week for two weeks, hence six sessions in total. Each session lasts 45 minutes. Based on the main study hypothesis, therapy for EG1 will embed MI training during physiotherapy, while EG2 will receive MI training after the physiotherapy part. For a detailed description please see Section 'Study intervention' on page 14. Baseline measurements will be repeated directly after the therapy session weeks to evaluate short-term effects of the MI intervention (T1), as well as after a follow up period of two weeks (FU). All intervention and assessment sessions will take place at the rehabilitation centre's physiotherapy department.

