#### Randomisation and allocation concealment

Patients will be randomly allocated to the study groups (EG1, EG2, CG) to ensure internal validity of results. Group allocation to one of the three study groups will be performed after the second baseline assessment (T0) using a randomisation list. The list has been generated with MATLAB 2007b (Mathworks Inc., USA) by a researcher not involved in the study. The generated list has been sent to the clinic's pharmacist, who is not involved in the study and will have no contact with study patients. The pharmacist will prepare sealed envelopes with the patient allocation based on the randomisation list. Patients will be given the sealed envelope by the treating therapist and they will open the envelop themselves. After opening, envelopes will be stored with the patient's personal documents in a locked cabinet. Only the treating therapist and the research assistant will have access to the documents. The independent examiner will not have access to the documents. Patients will be told not to talk to the examiner about the group allocation or therapy content during the post-intervention assessments. Randomisation will be concealed to the independent examiner until the last follow-up assessment of the patient has been performed.

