##### Group comparison

Group equality will be determined at baseline regarding all descriptive variables: age, gender, disease, affected brain hemisphere, time since stroke onset, cognitive function, handedness, rehabilitation history, patient's sports history, and patient's history of falls since stroke onset (over the last six to twelve months). Parametric and nonparametric tests will be used depending on statistical data level and data distribution. Furthermore, inter-group comparisons between BL and T0, T0 and T1, as well as T1 and FU will be calculated to analyse changes among all three groups over time. Additionally, intra-group comparisons for each measurement event (pre- and post-intervention; T0 vs. T1 vs. FU) will be calculated for all three groups; means, standard deviations and confidence intervals, will be given where feasible. An intention to treat analysis will be performed for drop outs. Missing values will be replaced by the average trend of all participants of the respective group.

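### The primary comparison uses the raw T0–T1 change in task time with no baseline covariate, although task time is measured twice before randomisation; adjusting T1 for baseline would normally be more precise

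*Protocol article*

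**What the plan says.** The section 'Primary outcome measure' states: "This primary outcome will be assessed by the difference between measurement points T0 and T1". Table 1 under 'Primary and secondary outcome measures' agrees ("Time difference between T0 and T1 needed to perform the motor task"), with time in seconds taken from video.

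Under 'Group comparison', "inter-group comparisons between BL and T0, T0 and T1, as well as T1 and FU will be calculated to analyse changes among all three groups". No covariate is named there or anywhere else. The only other baseline step is that "Group equality will be determined at baseline regarding all descriptive variables", and the list that follows does not include task time.

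Two pre-randomisation readings exist. 'Study procedure and measurement events' says: "During this time patients will undergo all clinical measurements twice (BL, T0) at an interval of six to seven days". 'Randomisation and allocation concealment' says: "Group allocation to one of the three study groups will be performed after the second baseline assessment (T0) using a randomisation list". BL task time appears only as a secondary outcome in 'Motor task related profile': "Time difference to perform the motor task between BL and T0 as well as between T1 and FU".

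'Statistical analyses' leaves the final method to be chosen once the data are in, from checks of normality and equal variances. 'Sample size calculation' gives no number of patients. No SD or correlation for task time is stated.

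**The concern.** A change score subtracts the whole of one T0 reading, which amounts to fixing the slope of T1 on T0 at 1. If the true slope is below 1, this has two consequences.

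- The between-group comparison carries more variance than it needs to, because the noise in the single T0 reading passes straight into the outcome and the BL reading is not used.
- If the arms happen to differ at T0, part of that difference stays in the realised estimate.

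At stake is precision for the EG1–EG2 contrast, the research question of the trial, in a three-arm pilot with no stated size. BL and T0 both precede randomisation, so both are legitimate covariates and both are already scheduled.

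**Working it through.** The plan has no figure to reproduce. The check compares the variance of the change score with the residual variance of T1 after baseline adjustment. All correlations, SD ratios and arm sizes below are assumptions.

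**1. Equal variances (set to 1), common correlation ρ among BL, T0 and T1.**

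- Change score: 2(1 − ρ)
- ANCOVA on T0: 1 − ρ²; reduction against change = (1 − ρ)/2
- ANCOVA on BL and T0: 1 − 2ρ²/(1 + ρ); ratio to change = (1 + 2ρ)/(2(1 + ρ)); reduction = 1/(2(1 + ρ))

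| ρ | Change variance | Reduction, T0 only | Reduction, BL and T0 |
|---|---|---|---|
| 0.5 | 1.0 | 25% | 33.3% |
| 0.6 | 0.8 | 20% | 31.2% |
| 0.7 | 0.6 | 15% | 29.4% |
| 0.8 | 0.4 | 10% | 27.8% |
| 0.9 | 0.2 | 5% | 26.3% |

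**2. Serial decay** (adjacent correlations ρ, BL–T1 correlation ρ²). BL adds nothing once T0 is in the model, so the reduction is (1 − ρ)/2: 25%, 15%, 10% and 5% at ρ = 0.5, 0.7, 0.8 and 0.9.

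**3. Mild decay** (BL–T0 = r, T0–T1 = r − 0.05, BL–T1 = r − 0.10). Adjusting for both gives 27.5%, 23.4%, 18.1% and 9.6% at r = 0.6, 0.7, 0.8 and 0.9.

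**4. Unequal SD at T1** (s times the baseline SD, common ρ). Change = s² + 1 − 2ρs; adjusted for both = s²[1 − 2ρ²/(1 + ρ)]. At ρ = 0.7 and s = 0.8: 0.52 against 0.271, a 48% reduction. At ρ = 0.7 and s = 1.2: 0.76 against 0.610, a 20% reduction. Over ρ = 0.5–0.9 the ranges are about 48–53% and 20–24%.

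**5. Cost of estimating the covariates.** The inflation factor is (N − g − 1)/(N − g − q − 1), with g = 3 arms and q covariates.

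- 10 per arm, q = 2: 26/24 = 1.083. The common-correlation reductions at ρ = 0.5, 0.7, 0.8 and 0.9 become about 28%, 24%, 22% and 20%.
- 20 per arm, q = 2: 56/54 = 1.037, giving about 31%, 27%, 25% and 24%.
- Least favourable case, serial decay with ρ = 0.9 and 10 per arm: with both covariates 0.95 × 1.083 = 1.029, about 3% worse than the change score. With T0 alone the factor is 26/25 = 1.04 and 0.95 × 1.04 = 0.988, about 1% better.

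**6. Mean of BL and T0 as a single covariate.** Under common correlation this equals using both. Under serial decay the residual variance is 1 − ρ²(1 + ρ)/2. At ρ = 0.9 that is 0.2305 against 0.2 for the change score, about 15% worse. The mean therefore lacks the large-sample guarantee that T0 as its own covariate has.

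**7. Chance imbalance.** With equal variances, a T0 difference of d between two arms shifts the expected difference in T1 − T0 by −(1 − ρ)d. That is 50% of d at ρ = 0.5, 30% at 0.7 and 10% at 0.9, in favour of the arm that was slower at T0. Averaged over randomisations d is zero, so the estimator is unbiased.

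**8. Separating scale from adjustment.** Simulated power with 15 per arm, log-SD 0.5, ρ = 0.7 and an effect of −0.35 on log time (1,500 trials, lognormal times):

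| Analysis | Power |
|---|---|
| Change in seconds, test chosen after normality and variance checks | 53% |
| Change in log seconds | 68% |
| Log ANCOVA on T0 | 72% |
| Log ANCOVA on BL and T0 | 78% |

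Of the 25-point gain, 15 points come from the log scale. Baseline adjustment adds 4 points with T0 and 10 with both. Under serial correlation of 0.7, T0 alone gives 70% and both give 68%.

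**The case against.** The strongest reply is that nothing here is an error. Randomisation makes the change-score comparison unbiased, and the article defines an outcome variable without prescribing an unadjusted test. The method is left open, covariates are often settled in a fuller document, and a change outcome is compatible with adjustment: regressing T1 − T0 on group and T0 gives the same group estimate as regressing T1 on group and T0.

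Much of this stands. The point is one of efficiency, and the text does not forbid a covariate. But the raw difference is written in as the primary outcome, the comparison described is of changes, and what is left open is the choice of test from distributional checks. None of that leads to baseline adjustment.

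Three stronger readings are tempting, and the documents do not support them.

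- A reader might infer that the estimate is biased. Only the realised estimate is shifted, given a chance T0 imbalance.
- A reader might infer a variance cut of a quarter to a third at no cost. That needs equal variances and a common correlation of about 0.5 to 0.9. BL and T0 are about a week apart and T1 follows two weeks of therapy, so decay is plausible. The covariates also use degrees of freedom.
- A reader might credit baseline adjustment with the whole rise in power from 53% to 78%. Most of it comes from changing the scale, in a simulation whose lognormal times and multiplicative effect suit the log model.

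Testing baseline characteristics for group equality is a separate reporting matter and does not alter the primary estimate.

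**Conclusion.** The point holds as an avoidable loss of precision. The primary comparison is set up on an unadjusted change, and a second pre-randomisation reading goes unused in it. In large samples, ANCOVA with T0 as its own covariate, with or without BL, is never less precise than the change score, because the change score is the special case with a slope of 1 on T0 and 0 on BL.

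The size cannot be fixed from the documents. Under equal variances it is a 26–33% reduction with both baselines if the correlation is common (0.5–0.9), and 5–25% with T0 alone. Under serial decay it is 5–25%, with nothing from BL. Estimating the covariates trims these figures in small arms, and in the least favourable case examined it cancels the gain from using both.

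**What to change.** State the primary between-group analysis as ANCOVA of T1 task time in seconds on group, with T0 as a covariate and preferably BL as a second one. Report the adjusted EG1–EG2 difference with its 95% CI. Fix the covariates before any outcome data are seen. If arms will be very small, T0 alone is the safer choice. The mean of BL and T0 saves a degree of freedom but relies on roughly equal correlations with T1. The T0–T1 change can still be reported descriptively.

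The cost is wording, plus one or two degrees of freedom. No measurement is added, and the effect stays a difference in seconds. Like the change score, the analysis needs a recorded time at T0 and T1; using BL also needs a time there.

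Treat log seconds as a separate decision. It turns the effect into a ratio of times, needs completed tasks, and should have its power gain reported apart from that of baseline adjustment.

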##### Secondary outcome measures

Secondary outcome measures have been categorised into four different profiles that utilise distinctive assessment types.

##### Motor task related profile

1. Time difference to perform the motor task between BL and T0 as well as between T1 and FU.

2. Help needed to perform the motor task will be evaluated using classification levels of the activity scale of the Chedoke McMaster Stroke Assessment (CMSA) [40,41]. The CMSA is a validated and very reliable performance-based assessment [42-44]. The activity scale belongs to the gross function index and is scored with one (patient needs total assistance or the task is not tested for safety reasons) to seven (patient can perform the task completely independent without any assistance or devices, in a reasonable time) on an ordinal scale [45].

3. Stage of the motor task will be evaluated using the classification of Bergland and Laake [46] (please see section 'Stages of the motor task').

4. 'Imagination inflation': Undergraduate college students overestimated their motor performance after MI training. This effect is called 'Imagination inflation' and was detected by Landau et al [47]. To monitor the inflation in this investigation all patients will be asked before each motor task execution during the assessments to predict time they will need to perform the task before each motor task execution.

##### Motor impairment and balance profile

The motor impairment and balance profile will be evaluated with the German versions of the extended Barthel index (EBI) and the Berg Balance Scale (BBS). Both assessments will take about 15 to 20 minutes each to complete.

5. The EBI is a 16-item performance-based measurement. Activities of daily living (ADL), e.g. personal hygiene, dressing, feeding, and cognitive aspects, e.g. communication and problem solving, will be scored on a five-point Likert scale (0 = cannot perform the task, 4 = independent) [42,48]. The total score will be used to evaluate trends. Validity and reliability were examined with patients after stroke and multiple sclerosis [49-52]. A validated German version is available [50].

6. The BBS consists of 14 items to assess two dimensions of balance impairments in (older) individuals and patients undergoing rehabilitation. The ability to maintain an upright posture in different positions and the ability to adjust posture when reducing support surface will be scored on a 5-point ordinal scale (0 to 4). High scores are interpreted as a sufficient ability to perform a task or to perform it within a given time frame [42,53]. The total score will be used to evaluate trends. Validity, reliability and sensitivity to change were evaluated [53-56]. A validated German version is available [57].

##### Motor imagery profile

The motor imagery profile will be assessed with the Kinesthetic and Visual Imagery Questionnaire (KVIQ) and the Imaprax software, version 1.1. The completion of both assessments will take 30 to 40 minutes.

7. The KVIQ includes a visual and a kinaesthetic imagery scale and was developed based on the revised movement imagery questionnaire (MIQ) [58]. The new measure was specifically developed to assess motor imagery ability for individuals with motor impairments in 2007 by Malouin et al. [59]. The questionnaire is available in a short (10 items) and a long version (20 items). The latter will be used in this investigation. All items will be evaluated in a standardised sequence while sitting for visual and kinaesthetic scales. The assessment requires performing a sequence of simple movements once, imagine the movement once and score the vividness of the 'inner picture' on a 5 point Likert scale (1 - 'image as clear as actually seeing it' to 5 'no image') as well as the feeling of the imagined movements (1 - 'as intense as making the movement' to 5 - 'no sensation'). The total score of each subscale will be used to evaluate trends.

8. The Imaprax 1.1 software was developed to evaluate understanding of MI, vividness of movement imagery, and imagery perspective in patients with apraxia following stroke. It is based on software that was used with skydivers [60,61]. Six gestures or activities will be evaluated in a three step standardised procedure: select the correct gesture or activity from three proposed ones, evaluate the vividness of the 'inner picture', and determine the internal or external perspective of your 'inner picture'. The total score of MI vividness will be used to evaluate trends.

KVIQ and Imaprax assessment tools were published in other languages than German. Following a cross-cultural translation and adaptation based on guidelines for self-report questionnaires by Beaton et al. [62] both assessments were forward translated into German. To check for consistency both tools were backward translated into their original publication languages and checked by the original authors. We obtained the permission from those authors to use the translated assessments in our study.

##### Psychological profile

The psychological effect of MI is not yet proven. Nevertheless, authors of published MI studies proposed to include assessments of selected psychological factors, e.g. attention and working memory [63]. The psychological profile includes the evaluation of patient's fear of falling (FOF) using the Activities-Specific Balance Confidence Scale (ABC-scale).

9. The ABC-scale is 16-item questionnaire that evaluates the self-confidence of a person based on Bandura's theory of self-efficacy [42,64]. It can be self-administered or completed during a face to face interview. Patients determine their self-perceived confidence to remain in balance on a visual analogue scale (VAS) ranging from zero to 100 percent (10 cm). The mean value will be used to evaluate trends. The scale is a valid and reliable assessment that is available in German language [65,66].

10. Furthermore, intrinsic motivation will be evaluated from the patient's MI diary. Using details on frequency of independent MI practice reported in the patient's diary motivation to practice and the compliance with the training can be determined [67]. Other investigations showed that patients regained self-control about their recovery process. They felt more skilful, and patients as well as athletes expressed their satisfaction and belief in the MI training, which helped to improve their performance [68,69].

11. Patient's mood will be enquired by a direct question: 'How do you feel today?'. This will be scored on an 11-point VAS ranging from zero (very good) to ten (very bad).

##### Further evaluations and assessments

To further describe the included study population the following descriptive data will be obtained from each participant: age, gender, weight, disease, affected side, time since stroke onset, actual medication, cognitive function, handedness, rehabilitation history (treatments until study start), patient's sports history, and patient's history of falls since the stroke onset (over the last six to twelve months). Data will be obtained by direct questions to patients, from medical records, and from a relative or proxy.

Cognitive function will be assessed with the Mini-Mental State Examination (MMSE). MMSE is a short screening tool for dementia symptoms [70]. MMSE includes items to evaluate spatial and temporal orientation, short-term memory, attention and calculation abilities, language, thinking, and action planning. The total score is 30 points. MMSE will be performed once at a baseline assessment and will take about 15 to 20 minutes.

Patient's handedness will be determined with the Edinburgh Handedness Inventory (EHI) once. The EHI is a valid and reliable short 10-item questionnaire. Patients will be asked what is the preferred hand to carry out activities of daily living (ADL), e. G. Using toothbrush, cut something with a scissor, or use a spoon [71]. The EHI will take about five to ten minutes to complete.

Further important information that may influence the effect of MI are:

- patient's type of learning (visual or kinaesthetic),

- patient's belief in the therapy [72].

Both will be assessed by direct questions during baseline measurement events.

